#### a. Carotid-femoral pulse wave velocity (cfPWV)

3.7.1

The right carotid to right femoral path length will be measured in a straight line with a tape ruler, and 80% of this distance used as pulse wave traveled distance (d).^[38]^ Right carotid-femoral transit time will be obtained by subtracting the time (t) between onset of the electrocardiographic R wave and the foot of the carotid pulse and the time between the R-wave and the femoral pulse, each averaged from 8 to 10 sequential waveforms. cfPWV will be calculated as d/t and expressed as m/s. Two measurements will be taken and averaged. If their difference exceeds 0.5 m/s, a third measurement will be made and the median value taken.

#### b. Pulse wave analysis

3.7.2

This is performed on the arm not used for vascular access. From the radial artery waveform obtained by the high-fidelity tonometer, the SphygmoCorPx System reconstructs the aortic pressure waveform using a transfer function.^[39,40]^ This waveform depends on left ventricular ejection, as well as the timing and amount of wave reflection from branch points or areas of impedance mismatch which are determined by aortic stiffness and arteriolar tone.^[41]^ From the aortic waveform, central systolic, diastolic, mean and pulse pressures are obtained. Aortic augmentation index (AI) will be calculated as the increment in pressure from the first systolic shoulder of the ascending aortic pressure wave to the peak of the second, late systolic shoulder, expressed as a percentage of the pulse pressure. Aortic AI is also normalized to a heart rate of 75 beats/min to facilitate comparison.

#### Multislice CT

3.7.3

Calcium scoring will be performed using a high-pitch multislice computed tomogram scanner. All patients should have a resting heart rate <100 beats/min. Scan length is defined by a scout view from the arch to the diaphragm. For all scans, the extent of CAC and AVC will be assessed using both volume and Agatston scores by 2 radiologists unaware of treatment assignment. The volume score will be determined by the calculated volume of calcified plaques with a density of > 130 Hounsfield units and a minimum size of 0.5 mm^3^ based on isotropic interpolation.^[42]^ The Agatston score will be calculated by multiplying the weighted value and size of the calcified areas as previously described.^[43]^

### Study outcomes

3.8

Control and intervention arms will be compared for the following outcomes of interest:

Primary outcome

Absolute difference in CAC score at 18-months

Secondary outcomes

(1)Absolute difference in AVC score at 18-months(2)Percentage of patients with regression of CAC of ≥ 10% over 18-month(3)Absolute difference in cfPWV and AI at 18-months(4)Mortality from any cause within the study period(5)MACE defined as non-fatal myocardial infarction, heart failure, acute coronary syndrome, need for coronary revascularization, non-fatal stroke, significant peripheral vascular disease (gangrene, amputation, need for revascularization) within the study period(6)Difference in plasma levels of dp-ucMGP at 18 months(7)Vascular access events, including clotting requiring insertion of a new dialysis catheter, declotting or exchange of an existing catheter, and vascular intervention during the study period.

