**Discussion::**

Evidence of successful regression or retardation of vascular calcification will support the conduct of larger and longer-term trials aimed at reducing cardiovascular disease mortality and major adverse cardiovascular events in this high-risk population using a safe and inexpensive strategy

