## Introduction

1

It is well recognized that coronary artery calcification (CAC), a form of vascular calcification (VC), occurs at a much higher rate in the dialysis population compared to age-matched populations without chronic kidney disease (CKD).^[1,2]^ Studies have also confirmed a positive association of CAC with adverse outcomes in this population.^[2]^ There is a dose relationship reported between the CAC score and cardiovascular disease (CVD) mortality; the higher the score, the higher the mortality risk.^[3]^ Given that one major cause of death and hospitalization in the dialysis population is CVD, these observations may be of critical importance in efforts to reduce CVD mortality and morbidity.^[2]^

Two distinct types of VC are reported in the CKD population.^[4]^ Atherosclerotic calcification occurs in the intimal layer and is associated with atherosclerosis and potentially rupture of unstable plaque, leading to acute myocardium infarction and stroke. Various animal models and human studies support the development of this form of VC in uremic and non-uremic settings. Another form, medial calcification (calcific arteriosclerosis) is also commonly observed in CKD and uremia, and contributes to a higher CVD mortality in this population due to increased vascular stiffness with loss of vessel elasticity, resulting in increased cardiac afterload, progressive left ventricular hypertrophy and ultimately, heart failure and arrhythmia.^[5]^

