**Figure 2 F2:**
[figure not shown]
Study schedule of assessment.

The criteria for termination of the study are:

(1)Withdraw consent(2)completion of the study protocol at 18 months(3)renal transplantation(4)mortality(5)requirement for Vitamin K antagonist(6)allergy to MK-7(7)parathyroidectomy(8)started on any vitamin K supplementation outside of clinical trial

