### Statistical methods

3.9

The absolute difference in CAC and AVC scores at 18-months between control and intervention arms will be compared using the t-test following log transformation. Adjustment for baseline CAC and AVC scores respectively will be made via the analysis of covariance. Likewise, the effects of MK-7 supplementation on dp-ucMGP level, CFPWV and AI at 18 months will be compared between the 2 groups using the t-test, with adjustment made for the respective baseline covariates via analysis of covariance.

The percentage of patients with regression of CAC score of ≥ 10% at 18 months from baseline will be compared between control and intervention arms via the χ^2^ test. The effect of treatment will be quantified using the odds ratio estimate and its associated 95% confidence interval. The logistic regression analysis will be used to account for potential confounders where applicable.

For all-cause mortality and MACE, the time to the respective event is defined as the time from randomization to the time when the event of interest occurred. Subjects in whom an event was not observed will be censored at 18-months. The Kaplan-Meier survival analysis and the log-rank test will be used to compare the survival distributions between the control and intervention groups. The effect of treatment will be quantified using the hazard ratio estimate and its associated 95% confidence interval. Further, the Cox proportional hazards regression stratified by diabetes will be used to account for potential confounders where applicable.

All statistical evaluations will be made assuming a 2-sided test at the 5% level of significance based on an intention-to-treat analysis.

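### The MACE composite leaves out fatal stroke and sudden cardiac death, and the censoring rule carries those patients as MACE-free to 18 months, so the MACE hazard ratio can move against the arm with fewer deaths

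*Protocol article*

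**What the plan says.** Three places in the protocol article fix this point.

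- **Section 3.8, Study outcomes, secondary outcome 5.** The composite is "MACE defined as non-fatal myocardial infarction, heart failure, acute coronary syndrome, need for coronary revascularization, non-fatal stroke", followed by "significant peripheral vascular disease (gangrene, amputation, need for revascularization) within the study period". Infarction and stroke are limited to non-fatal events. Heart failure and acute coronary syndrome have no such limit. Cardiovascular death is not listed.
- **Section 3.8, secondary outcome 4.** Death is a separate outcome: "Mortality from any cause within the study period".
- **Section 3.9, Statistical methods.** One rule covers mortality and MACE: "Subjects in whom an event was not observed will be censored at 18-months". The analysis is then the same for both: "The Kaplan-Meier survival analysis and the log-rank test will be used to compare the survival distributions between the control and intervention groups", with a hazard ratio and a Cox model stratified by diabetes. No separate rule covers a patient who dies before any MACE.

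Deaths are expected. The termination criteria listed with Figure 2 include "3)renal transplantation(4)mortality(5)requirement for Vitamin K antagonist", and the Introduction gives the reason to expect cardiovascular ones: "Given that one major cause of death and hospitalization in the dialysis population is CVD".

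**The concern.** A patient whose first cardiovascular event is a fatal stroke or a sudden cardiac death has no event in the composite and can never have one afterwards. Death is thus a competing event for MACE. Two consequences follow.

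1. **Definition.** Whether an event counts depends on whether the patient survives it. An arm in which more patients survive their first event can record more MACE.
2. **Censoring.** Taken literally, the rule keeps a dead patient in the MACE risk set until month 18. That patient adds event-free follow-up that was never lived, which lowers the apparent MACE hazard in the arm with more deaths.

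Both push the MACE hazard ratio the same way, against the arm with fewer deaths. The comparison matters because the abstract's discussion looks ahead to "larger and longer-term trials aimed at reducing cardiovascular disease mortality and major adverse cardiovascular events in this high-risk population", and the MACE estimate here is natural input to planning such trials.

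**Working it through.** **The plan's own figure.** The only sample-size figure is for the calcification score: log difference 6.91 − 6.67 = 0.24, SD 0.55, 80% power, two-sided 5%. This gives 83 per arm (84 with the t-distribution) against the stated 85, and 170/0.85 = 200. It reproduces, and it has no bearing on MACE. The document states no MACE rate, death rate or MACE power, so everything below is an illustration on assumed rates.

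**Assumptions.** Over 18 months in the control arm, MACE as defined occurs first in m₀ = 10% to 20% of patients, and a fatal cardiovascular event outside the composite occurs first in f₀ = 5% to 15%. Hazards are constant, nobody leaves for other reasons, and non-cardiovascular deaths are set aside.

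**Hazard ratio under the rule as written.** With dead patients kept at risk to 18 months, HR = ln(1 − m₁)/ln(1 − m₀).

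**Scenario A: fatal first events become survived ones.** A share c = 30% to 50% of fatal first events becomes non-fatal, so m₁ = m₀ + c·f₀ and f₁ = (1 − c)·f₀.

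| f₀ → f₁ | m₀ → m₁ | HR as written | MACE or CV death |
|---|---|---|---|
| 5% → 3.5% | 20% → 21.5% | 1.08 | 25% vs 25% |
| 10% → 5% | 20% → 25% | 1.29 | 30% vs 30% |
| 15% → 7.5% | 10% → 17.5% | 1.83 | 25% vs 25% |

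The first and last rows are the extremes of the grid. In the middle row, ln(0.75)/ln(0.80) = 0.2877/0.2231 = 1.29, although cardiovascular deaths are halved and total events are equal.

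**Does correct censoring alone cure scenario A?** No. With censoring at death the hazard ratio is cause-specific. The total hazard is the same in both arms, so it equals m₁/m₀. In the middle row that is 25/20 = 1.25 instead of 1.29. Most of the distortion comes from the definition, and only a composite that includes death returns 1.00.

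**Scenario B: fatal first events are prevented and the MACE hazard is unchanged.** This isolates the censoring rule. Take f₀ = 10%, m₀ = 20%.

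- Control total hazard: −ln(0.70) = 0.3567, split into MACE 0.3567 × 20/30 = 0.2378 and fatal 0.1189.
- Halve the fatal hazard: total 0.2378 + 0.0595 = 0.2972 (from unrounded values).
- Treated MACE: (0.2378/0.2972) × (1 − e^(−0.2972)) = 0.80 × 0.2571 = 20.57%.
- HR as written: ln(0.7943)/ln(0.80) = 1.03. The cause-specific ratio is 1.00.

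Across the same grid, with a 30% to 50% reduction in the fatal hazard, the ratio as written runs from 1.01 to 1.05.

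**What the literal rule estimates.** If death were the only reason to leave early, keeping dead patients at risk to 18 months would make one minus Kaplan-Meier equal the cumulative incidence of MACE, and the hazard ratio would be of subdistribution type. The plan does not say that this is intended. The rule also carries forward patients who leave alive, for example through withdrawal of consent, and for them there is no such justification.

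**The case against.** The strongest points on the other side, and what stands of each:

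- **Fatal infarction may be counted.** Acute coronary syndrome is unqualified and infarction is a form of it. A reader might infer that every fatal infarction is scored as no MACE, but the text does not settle that. The word non-fatal before infarction points one way and the unqualified syndrome the other. Fatal stroke and sudden cardiac death have no such route in.
- **Deaths are captured.** All-cause mortality has its own time-to-event analysis, and reporting death beside a morbidity composite is a recognised choice that avoids judging cause of death in an open-label trial. A reader might infer that the plan treats the worst outcome as a good one. It does not do so for the trial as a whole, because every death counts in outcome 4. The MACE hazard ratio itself remains uncorrected.
- **The harm scenario is constructed.** Scenario A needs events to be converted, not prevented. The proposed mechanism, slower calcification, would be expected to lower fatal and non-fatal events together. This stands, and it is why scenario B is shown.
- **It would not reach significance.** With 100 per arm, 25% against 20% gives z = 0.05/√(0.225 × 0.775 × 2/100) = 0.85, p about 0.40. This stands. The issue is a misleading point estimate, not a likely false-positive test.
- **Competing-risk methods belong in an analysis plan.** Their absence alone would be no finding. Here, though, the article states a composite and a censoring rule, and both are open to the reading above. The censoring sentence may be shorthand, in which case rewording it is easy.

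**Conclusion.** The point holds for fatal stroke and sudden cardiac death, and as an ambiguity for fatal infarction. Followed as written, the plan gives a MACE curve and hazard ratio in which death before MACE counts as event-free time to month 18, and the estimate can move against the arm with fewer fatal events. On the assumed rates the distortion is a hazard ratio of 1.08 to 1.83 if fatal events are converted to survived ones, and about 1.01 to 1.05 if they are simply prevented. The documents give no rates with which to choose between these, and do not show that MK-7 would convert events.

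The point is confined to one unpowered secondary outcome. The calcification result and the mortality comparison are unaffected. It deserves correction because it is cheap to correct and the MACE estimate may inform later trials.

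**What to change.** Settle the following before the comparative MACE analysis:

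1. **Censoring.** Replace the 18-month rule for MACE with censoring at the earliest of death, last contact or 18 months. Report a cause-specific hazard ratio, and show cumulative incidence (Aalen-Johansen) with death as a competing event in place of one minus Kaplan-Meier.
2. **Added analysis.** Beside the composite as published, report time to first MACE or death from any cause. Both parts are already outcomes, so no new data and no cause-of-death judgement are needed. Item 1 alone would not remove the distortion in scenario A. This item does.
3. **Cardiovascular death.** Use MACE plus cardiovascular death only if cause can be classified blind to arm. The article does not say that cause of death is classified.
4. **Definition.** State whether a fatal infarction counts under acute coronary syndrome.

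Section 5 says that all final visits are complete, and the trial is open-label. Item 2 should therefore be dated and labelled as supplementary, and should not replace the published composite.

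The cost is one extra analysis and a few sentences of text. Non-cardiovascular deaths will dilute the added composite, and it overlaps with the mortality outcome.

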### Statistical methods

3.9

The absolute difference in CAC and AVC scores at 18-months between control and intervention arms will be compared using the t-test following log transformation. Adjustment for baseline CAC and AVC scores respectively will be made via the analysis of covariance. Likewise, the effects of MK-7 supplementation on dp-ucMGP level, CFPWV and AI at 18 months will be compared between the 2 groups using the t-test, with adjustment made for the respective baseline covariates via analysis of covariance.

The percentage of patients with regression of CAC score of ≥ 10% at 18 months from baseline will be compared between control and intervention arms via the χ^2^ test. The effect of treatment will be quantified using the odds ratio estimate and its associated 95% confidence interval. The logistic regression analysis will be used to account for potential confounders where applicable.

For all-cause mortality and MACE, the time to the respective event is defined as the time from randomization to the time when the event of interest occurred. Subjects in whom an event was not observed will be censored at 18-months. The Kaplan-Meier survival analysis and the log-rank test will be used to compare the survival distributions between the control and intervention groups. The effect of treatment will be quantified using the hazard ratio estimate and its associated 95% confidence interval. Further, the Cox proportional hazards regression stratified by diabetes will be used to account for potential confounders where applicable.

All statistical evaluations will be made assuming a 2-sided test at the 5% level of significance based on an intention-to-treat analysis.

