### Eligibility criteria:

3.2

Patients meeting the inclusion and exclusion criteria will be invited to participate and written informed consent obtained for those willing to participate. Consented subjects will attend a screening visit (V0) where a multislice computed tomogram will be performed to assess their degree of CAC. As the main objective is to investigate the effects of intervention on VC, pre-existing CAC indicated by a baseline CAC score of ≥ 30 Agatston units is mandated for entry into the trial. This threshold also excludes patients with mild CAC which is unlikely to progress in the relatively short window of observation.^[19]^ Other inclusion and exclusion criteria are outlined in Table 1. Consent is taken by study team co- investigator after detailed explanation of purpose, benefit and risk of the study. Witness is required for patient signing informed consent in Chinese and Malay language. Patients are informed the right to withdraw consent and participation at any time during the study period.

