### Sample size

3.4

To ensure that the study is adequately powered, we have estimated the sample size based on the primary outcome of absolute difference in CAC score at 18-months between the control and intervention arms, assuming mean CAC scores at 18-months of 1005 and 786 respectively as reported by Block et al.^[19]^ Applying natural logarithmic transformation to CAC scores due to skewed distribution, this corresponds to a mean logCAC of 6.91 and 6.67, respectively. Further assuming a common SD of 0.55, power of 80%, 2-sided level of significance of 5% and equal allocation between the 2 treatment arms, a minimum sample size of 170 in total, or 85 per arm will be required. Accounting for an attrition rate of 15%, we will recruit a total of 200 patients.

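### CAC regression, mortality and MACE are compared without baseline CAC, a prognostic value every patient has before randomization; the tests are valid but may give up some power

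*Protocol article*

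**What the plan says.** Protocol article, Section 3.9 (Statistical methods), by type of outcome:

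- **Continuous outcomes** (CAC, AVC, dp-ucMGP, cfPWV, AI): t-test, with analysis of covariance on the respective baseline.
- **CAC regression of at least 10%**: chi-square test and an odds ratio with its confidence interval. Then: "The logistic regression analysis will be used to account for potential confounders where applicable". No covariate is named.
- **All-cause mortality and MACE**: Kaplan-Meier curves, log-rank test and a hazard ratio. Then "the Cox proportional hazards regression stratified by diabetes will be used to account for potential confounders where applicable". Diabetes is fixed as the stratum and nothing else is named.

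Three other places bear on this. Section 3.2 makes a baseline score an entry condition: "pre-existing CAC indicated by a baseline CAC score of ≥ 30 Agatston units is mandated for entry into the trial". The Introduction says of CAC and cardiovascular mortality: "the higher the score, the higher the mortality risk". Section 3.3 stratifies randomization by diabetes status only, so baseline CAC is not balanced by design.

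**The concern.** The plan uses the baseline value where the outcome is continuous and leaves it out of the named comparisons where the outcome is binary or time-to-event. Yet baseline CAC is known for every patient before randomization, and the protocol itself treats it as a predictor of cardiovascular death. It is also the denominator of the regression outcome: a 10% fall is 3 units at a score of 30 and 100 units at a score of 1000, so the chance of meeting the criterion may depend on where a patient starts.

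Omitting a prognostic covariate from a logistic or Cox analysis leaves the test valid. It does move the estimated ratio towards 1 compared with the ratio conditional on that covariate, and it lowers power. The rationale given for the adjusted models, accounting for confounders, does not fit a randomized comparison. There, covariates serve to use prognostic information and should be fixed in advance. At stake is the sensitivity of three secondary comparisons in a trial sized for a different outcome.

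**Working it through.** **1. The plan's own figure.** Section 3.4 gives "this corresponds to a mean logCAC of 6.91 and 6.67, respectively" and "Further assuming a common SD of 0.55, power of 80%, 2-sided level of significance of 5% and equal allocation between the 2 treatment arms". The difference is 6.91 − 6.67 = 0.24.

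n per arm = 2 × (1.96 + 0.84)² × 0.55² / 0.24² ≈ 83 (normal approximation), or 83.4, rounded up to 84, with the t distribution.

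That is 166 to 168 in total, against "a minimum sample size of 170 in total, or 85 per arm will be required". With 15% attrition, 170 / 0.85 = 200. The figure reproduces. It concerns log CAC and says nothing about power for the three outcomes here.

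**2. Assumed inputs.** The documents give no event rates, no regression rate and no strength of association with baseline CAC. All power figures below come from simulations under assumed values, with one standardized baseline covariate standing for log CAC. Tests are two-sided at 5%.

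**3. Logistic model.** 170 patients; 15% regression in the reference arm at mean baseline; treatment odds ratio 2.75 (log 1.01); 2,000 runs.

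| Log odds per SD (OR) | Power without | Power with | SE without | SE with | Log OR without | Log OR with |
|---|---|---|---|---|---|---|
| 0 (1.00) | 76.4% | 76.8% | 0.383 | 0.386 | 1.017 | 1.025 |
| 0.3 (1.35) | 75.9% | 77.3% | 0.382 | 0.388 | 1.001 | 1.023 |
| 0.7 (2.01) | 73.8% | 77.0% | 0.370 | 0.391 | 0.933 | 1.018 |
| 1.0 (2.72) | 69.9% | 75.2% | 0.361 | 0.400 | 0.882 | 1.043 |

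In the last row the standard error rises with adjustment, but the estimate rises more: 0.882 / 0.361 = 2.44 without and 1.043 / 0.400 = 2.61 with. On the ratio scale, exp(0.882) = 2.42 against exp(1.043) = 2.84. The gain is in power, through the conditional ratio, and not in the standard error.

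**4. Cox model.** 200 patients; 18 months; treatment hazard ratio 0.5; 600 runs.

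| Control event risk | Log HR per SD (HR) | Power without | Power with | SE without | SE with |
|---|---|---|---|---|---|
| about 15% | 0.3 (1.35) | 35.0% | 35.5% | 0.455 | 0.457 |
| about 15% | 0.7 (2.01) | 30.7% | 30.2% | 0.459 | 0.464 |
| about 30% | 0.3 (1.35) | 62.0% | 64.2% | 0.310 | 0.312 |
| about 30% | 0.7 (2.01) | 51.2% | 59.2% | 0.320 | 0.321 |

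With 600 runs, the simulation error of one power figure is about √(0.5 × 0.5 / 600) = 2 points, so half-point differences mean nothing.

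**5. Other assumed settings.**

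- Cox, 100 per arm, hazard ratio 0.55, 40% control events: 64% to 66% (HR 1.5 per SD) and 59% to 66% (HR 2.0 per SD). With 20% control events: 35% to 35% and 32% to 36%.
- Logistic, 85 per arm, 20% regression in controls, odds ratio 2.5: 70% to 73% (OR 2 per SD) and 60% to 67% (OR 3 per SD).
- A separate run with strongly prognostic CAC gave 61.8% to 70.5% (Cox, 8.7 points) and 60.7% to 68.8% (logistic, 8.1 points). With CAC not prognostic, the two analyses were within about half a point (Cox 35.5% and 35.0%; logistic 75.7% and 75.1%).

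**6. Error rate under no effect.** In the simulations of steps 3 and 4, the adjusted tests rejected in 4.7% to 5.4% of logistic runs and 3.7% to 6.0% of Cox runs. Adjustment does not disturb the 5% level.

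**7. Chance imbalance.** With 100 per arm, the 95% limit for the factor by which imbalance in baseline CAC shifts an unadjusted hazard ratio is about exp(1.96 × √(2/100) × ln HR per SD). This is 1.12 at 1.5 and 1.21 at 2.0.

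**The case against.** The case against is substantial, and much of it stands.

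- **Covariate lists belong in an analysis plan.** This is a condensed article and that plan is not shown. So the missing list for the supplementary models is not the point made here. The point is the choice of unadjusted comparisons, which the article does state.
- **The chi-square and log-rank tests are named in advance and valid.** This stands. Ordinary sampling error also dwarfs chance imbalance: with about 20 against 12 events, the 95% factor is exp(1.96 × √(1/20 + 1/12)) = 2.05, against 1.12 to 1.21, and the unadjusted interval already allows for such variation.
- **The prognostic strength is assumed.** This stands. The quoted relation is with cardiovascular mortality, while the outcomes are all-cause mortality and a broad MACE composite. No statement says that baseline CAC predicts 10% regression. A covariate also leaves the definition of that outcome, already relative to baseline, unchanged.
- **A late switch of analysis is itself flexibility.** Section 5 says all patients have completed their final visit in an open-label trial. This limits the fix to a decision recorded before the outcome comparison.

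Two stronger readings are tempting. A reader might infer that precision is lost. The tables do not support that for odds or hazard ratios. The precision argument fits continuous outcomes, where the plan already uses analysis of covariance. A reader might also infer that covariates will be picked after the data are seen. The wording does not exclude it, but nothing states it. Simulated worst cases, taking the most favourable model over all subsets of four candidate covariates, gave null rejection of about 7.6% to 11.6%. That applies only if such a model replaced the named tests, which the article does not propose.

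**Conclusion.** The point holds as a minor improvement. Section 3.9 uses the baseline for continuous outcomes and leaves baseline CAC out of the named comparisons for CAC regression, mortality and MACE. Those comparisons are valid. What they may forgo is about 0 to 9 points of power, with ratios nearer 1 than the conditional ones, if baseline CAC carries a hazard ratio of 1.5 to 2.0 or an odds ratio of 2 to 3 per SD. If CAC is weakly prognostic the difference is near zero, and the adjusted analysis then costs nothing material. Every power figure rests on assumed event rates and associations, and the primary outcome is untouched. The documents do not support a claim of inflated error or of covariates actually selected after the fact.

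**What to change.** In Section 3.9, or in a dated analysis plan completed before the outcome comparison between arms, state that:

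- the treatment effect on CAC regression of at least 10% is estimated by logistic regression with treatment, log baseline CAC and diabetes (the randomization stratum, which the logistic model does not name at present);
- the effects on mortality and on MACE are estimated by Cox regression with treatment and log baseline CAC, stratified by diabetes as already planned;
- the chi-square and log-rank results are reported alongside;
- any further covariate adjustment is exploratory, replacing the open reference to confounders.

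If the arms have already been compared on these outcomes, the unadjusted tests should stay as the main results and the adjusted models be labelled as added later.

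The cost is a few sentences and one degree of freedom per model for log CAC (plus one for diabetes in the logistic model). The baseline scores are already collected. The small downside is that the odds and hazard ratios become conditional on baseline CAC and should be described as such.

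### Censoring every event-free patient at 18 months credits withdrawn or lost patients with follow-up that was not observed, in the mortality and MACE analyses

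*Protocol article*

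**What the plan says.** Section 3.9 (Statistical methods) of the protocol article sets the same rule for all-cause mortality and MACE. On event times: "the time to the respective event is defined as the time from randomization to the time when the event of interest occurred". On everyone else: "Subjects in whom an event was not observed will be censored at 18-months". The analysis is then conventional: "The Kaplan-Meier survival analysis and the log-rank test will be used to compare the survival distributions between the control and intervention groups". A hazard ratio is reported, and "the Cox proportional hazards regression stratified by diabetes will be used to account for potential confounders where applicable".

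Three other places bear on this:

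- Section 3.4 (Sample size): "Accounting for an attrition rate of 15%, we will recruit a total of 200 patients".
- Section 3.2 (Eligibility criteria): "Patients are informed the right to withdraw consent and participation at any time during the study period".
- Section 3.5 (Study workflow, after Figure 2), under the words "The criteria for termination of the study are", lists withdrawal of consent, completion at 18 months, and then: "3)renal transplantation(4)mortality(5)requirement for Vitamin K antagonist(6)allergy to MK-7(7)parathyroidectomy(8)started on any vitamin K supplementation outside of clinical trial".

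The MACE definition in section 3.8 is made up of non-fatal and procedural events. Death is not a component.

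**The concern.** A censoring time should be the last time at which the patient was known to be event-free. Section 3.9 gives one fixed time to all event-free patients, while sections 3.2, 3.4 and 3.5 expect some to leave before it. The list in section 3.5 places the early reasons beside death and completion of the protocol, so it reads as a list of ways participation ends, and not only treatment. The article does not say that vital status or MACE is ascertained after that point.

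If the rule is followed literally, the risk sets contain patients whom nobody is observing. Events they have after leaving go unrecorded while their time counts as event-free. The Kaplan-Meier event risk is then too low. If one arm loses more patients, that arm looks better than it is. This is a stated rule that gives the wrong result, which is different from a detail left to a fuller document.

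**Working it through.** **Inputs from the protocol.** Horizon T = 1.5 years; attrition 15%; censoring rule as quoted. The attrition figure reproduces: 170 / (1 − 0.15) = 200.

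**Assumed inputs.** The protocol gives no event rate for mortality or MACE, no timing of loss and no split of loss between arms. The base case is a constant event rate λ = 0.15 per year, with a share p of patients assigned leaving times spread evenly over 18 months, independent of event risk. No events are captured after leaving.

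**Step 1: true 18-month risk.** F = 1 − exp(−λT) = 1 − exp(−0.225) = 20.1%.

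**Step 2: risk seen in a leaver.** Averaged over even leaving times, L = 1 − F/(λT) = 1 − 0.2015/0.225 = 10.5%.

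**Step 3: risk shown under the rule.** Nobody is censored before 18 months, so one minus Kaplan-Meier at 18 months is the proportion with an observed event, (1 − p)F + pL.

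| Non-death loss p | Risk shown (true 20.1%) |
|---|---|
| 5% | 19.7% |
| 10% | 19.2% |
| 15% | 0.85 × 20.1 + 0.15 × 10.5 = 18.7% |

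At p = 15% and other assumed rates, the same formula gives 10.5% shown against 11.3% true (λ = 0.08) and 24.1% against 25.9% (λ = 0.20). With exponential leaving times instead, true risks of 10%, 20% and 30% appear as 9.2%, 18.5% and 27.8%.

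**Step 4: hazard ratio when the true ratio is 1.00.** For 20% loss in the active arm and 10% in control:

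- active: 0.80 × 20.15 + 0.20 × 10.45 = 18.2%
- control: 0.90 × 20.15 + 0.10 × 10.45 = 19.2%
- ratio of cumulative hazards: ln(1 − 0.1821) / ln(1 − 0.1918) = 0.94

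Solving the Cox score equation under the same inputs gives 0.946.

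| Loss, active vs control | Null hazard ratio under the rule |
|---|---|
| 15% vs 15% | 1.00 |
| 20% vs 10% | 0.94 to 0.95 |
| 25% vs 5% | 0.89 to 0.90 |
| 10% vs 20% | about 1.06 |

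With a true ratio of 0.70 and exponential leaving, equal 15% loss leaves it at 0.70, and 20% versus 10% moves it to 0.66.

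**Step 5: censoring when follow-up ends.** Under the same independence assumption this recovers the true risk and the true ratio in every setting. If leaving is related to event risk, no choice of censoring date removes the bias entirely.

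**Step 6: death before MACE.** Suppose 16% die evenly over 18 months, with nobody otherwise lost and a MACE rate of 0.15 per year. Carrying deaths to 18 months gives 0.84 × 20.15 + 0.16 × 10.45 = 18.6%, which is the actual cumulative incidence of MACE. Censoring at death makes one minus Kaplan-Meier equal 20.1%, about 1.5 points above the proportion who actually have MACE.

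**The case against.** **The sentence may only name the administrative horizon.** The analysis is intention-to-treat, the end-of-study visit is scheduled for all study subjects, and patients remain under usual care, so events might be known to 18 months for many who stop early. If so, 18 months is the right censoring time for those patients. This limits the point to patients whose status is not known to 18 months, but does not remove it. Intention-to-treat fixes the arm, not the length of follow-up, and no section provides for ascertainment after participation ends.

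**A reader might infer that early deaths are miscounted in both analyses.** They are not. In the mortality analysis death is the event. For MACE, Step 6 shows that carrying deaths to 18 months approximates cumulative incidence, while censoring at death overstates absolute risk. That part is an unstated competing-risk choice and not an arithmetic error. Still, section 3.9 plans ordinary Kaplan-Meier and Cox without naming the quantity meant.

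**A reader might infer bias in favour of MK-7.** The documents do not support a direction. MK-7 allergy can end participation only in the active arm, but starting outside vitamin K could remove controls in an open-label trial, and section 4 (Discussion) notes that vitamin K preparations are sold over the counter.

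**The 15% may include deaths.** In section 3.4 it inflates the sample for an 18-month scan, which death also prevents. Non-death loss may then be well below 15%, and the 5% and 10% rows are closer. This stands.

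**The effect is small against sampling error.** With about 37 events (200 × 18.7%), the standard error of the log hazard ratio is about 2/√37 = 0.33. A ratio of 0.95 is a shift of 0.051, or about 0.16 standard errors. This also stands.

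**Conclusion.** The rule is wrong as written for patients who withdraw or are lost before 18 months, in both the mortality and the MACE analyses. The understatement of 18-month risk is about 1.5 percentage points at 15% non-death loss and 0.15 events per year, and about 0.5 points at 5% loss. It follows whenever leavers' later events are not captured. Bias in the hazard ratio needs unequal loss, which is plausible but not shown, and its sign cannot be predicted. All sizes rest on assumed event rates and on leaving that is independent of risk.

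The point concerns secondary outcomes only and is unlikely by itself to reverse a conclusion. The primary analysis of coronary calcification at 18 months does not use this rule. It merits correction because the text is explicit and the remedy is simple, but it is not a threat to the trial.

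**What to change.** Replace the censoring sentence in section 3.9 with: *Subjects without the event are censored at the earlier of the last date known to be event-free and 18 months after randomization.* Keep 18 months for those whose status is known to that point, including patients who stopped treatment but were still followed. State whether deaths and MACE are ascertained after early termination.

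For MACE, treat death without prior MACE as a competing event. Report absolute risk as cumulative incidence (Aalen-Johansen) and the treatment effect as a cause-specific hazard ratio with censoring at death, labelled as such.

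The cost is a few sentences in the analysis plan and one added estimator. It needs a last-known-status date for each early leaver. The article does not say whether these dates were recorded, so this should be checked. Section 5 (Study status) reports that final visits are complete and biomarker analysis is pending, so the change may still be possible before the final analysis.
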